## Methods

### Study design

The current study, intensive longitudinal assessment of stress and stress-related behaviors across a behavioral intervention or *INSTANT*, is a prospective observational cohort of individuals enrolled in a community-based weight loss program. The University of Kansas Medical Center Institutional Review Board (IRB) approved this study in May 2024 (IRB#:00160436) and registered with ClinicalTrials.gov in October 2024 (NCT06668259). The current protocol follows the reporting guidelines for EMA studies (See S1 Table). This study was approved by the local IRB prior to study implementation, and in compliance with US Federal Regulations and local IRB policies, this study undergoes annual IRB review with an extension provided on at least an annual basis.

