### Participants, eligibility, and recruitment

This study seeks 50 individuals who are newly enrolled in a community-based weight loss program centered in a metropolitan area of a Midwest state. Participants will be recruited from an existing 6-month-long community-based weight management program hosted by the University of Kansas Medical Center, local Diabetes Prevention Programs and other behavioral weight loss programs in the local area that may range from 6 to 12-months long. These weight management programs typically include trained health educators, 1-hour weekly video meetings, group peer support, structured nutrition plan (low calorie diet), personalized activity recommendations, and behavior change modifications [15]. Prospective participants will be recruited at their initial consultation or orientation visit for their behavioral weight loss program. Flyers will also be presented to participants at their initial visit. Measures were planned to coincide with initial enrollment (week-0), early weight change (week-6), and later weight change measures (week-12, week-26).

To be included, participants must be newly enrolled or plan to enroll in a community-based weight management program, must be over 18 years of age, have body mass index (BMI) ≥30 m/kg^2^, own a smartphone and be willing to download the mobile application to receive text messages [16]. Participants who chose to cease their community-based weight management program involvement after enrolling in the INSTANT study can still participate in later assessments, improving upon past studies which only included individuals who completed their program [17,18]. Indeed, stress may impact continued engagement in a weight management program. Participants will be excluded for being currently prescribed FDA-approved medications for weight loss, treatment for a medical condition that could affect body weight, or impacting stress levels (e.g., antidepressants), a current psychological condition that is untreated, hospitalization for a psychological condition within the past 12-months, or not being on a stable dose of treatment for at least 6-months. Other exclusion criteria are not being fluent in writing or speaking the English language, mobility limitations so they are unable to perform physical activity, and a family member who was previously enrolled or is currently enrolled in the study.

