The signal contingent survey includes eight questions total. First, participants will be asked a 1-question item to assess routine and disorder within the moment adapted from the Confusion, Hubbub and Order Scale [29]. Then, participants will complete the PANAS scale as described previously. Finally, participants will be queried where they are located (e.g., home, work) and who they are with (alone, friends, etc.) to address context.

The evening survey includes 11 questions. First, participants will report overall daily stress, and then indicate transient stressors, including home, school, job, conflicts with partner or children, and financial stress using checklist options [30]. This will be followed with four questions related to home chaos that demonstrated high validity and reliability in a previous adult sample (Cronbach’s alpha = 0.79, re-test reliability, r = 0.82) [31]. Then, participants will be asked if they engaged in moderate to vigorous physical activity, and if so, how many minutes during the day. These questions were based off primary questions the Godin-Shephard leisure questionnaire which has been validated in adults [32]. Survey burden will be assessed using a 1-item question at the end of the survey. Participants will be queried to the burden of completing the survey that day, with a scale of 1–5, with a higher score indicating it was very burdensome.

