#### Demographics and program attendance.

Participants will report demographic characteristics (e.g., age, race/ethnicity, income) and previous weight loss history at baseline. Enrollment in the program will be queried from the respective programs at initial screening to confirm meeting inclusion criteria. Final session attendance dates will be queried from the program at end of study.

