#### Stipends and incentives.

Participants will be paid up to 300 USD for completing the study, including 50 USD for each visit. Participants will also be eligible for a reduce initiation fee for the existing 6-month-long community-based weight management program hosted by the University of Kansas Medical Center. For completing Visit 1, participants will be given a wearable device (estimated value 100 USD). These devices can be used during the accelerometer wear periods. However, participants will be told to prioritize wearing the accelerometer during the selected periods.

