### Analytical approach

#### Aim 1: Examine the association between variability in individual stress and weight change.

For hypothesis 1a, that high variability in daily stress will be related to less weight loss, linear regression will examine week-0 average and change frequency in daily stress (morning survey) with weight change at week-12 (visit 3) and week-26 (visit 4). For hypothesis 1b, that high variability in daily stress will be related to less physical activity and sleep, multi-level models with logit link function (and binomial distribution) will be used to examine association between week-0 morning stress and same day MVPA and sleep, with an interaction of time/day*morning stress. For exploratory analyses, we will examine the associations of daily stress with MVPA and sleep at other time points (week-6, week-12, and week-26), lagged day effects of stress (i.e., stress on day 1 influencing MVPA and sleep on day 2) to preserve temporal ordering and considering inverse probability weighted marginal structural models, and the outcome of weight change at week-6.

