#### Aim 2: Examine the association between variability in coping and positive affect and weight change.

To address hypothesis 2, that high variability in coping and positive affect will be related to less weight loss, linear regression will examine week-0 average and change frequency in coping (morning survey) and positive affect (within day survey) with weight change at week-12 and week-26.

Potential covariates for both models include number of ACEs, program compliance (i.e., number of sessions attended), coping mechanisms (number and type), age, and sex. Statistical significance will be set at *p* = 0.05. All available data will be analyzed with a sensitivity analysis for individuals with complete data. Significant weight loss will be seen at 12-weeks (12.7 ± 19.9 kg), and 6-months (12.7 ± 35.2 kg) based on past studies in our community-based weight loss program allowing us to compare weight loss in Hypothesis 1a and 2. [15]

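### The covariates named for the weight models omit income, a baseline variable already collected, but include sessions attended, which accrue after the exposure

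*Protocol article*

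**What the plan says.** Under Study design, the Protocol article states that the study "is a prospective observational cohort of individuals enrolled in a community-based weight loss program". The exposure is therefore not randomised.

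Under Analytical approach, Hypotheses 1a and 2 are tested by linear regression of weight change at weeks 12 and 26. The regressors are the week-0 average and the change frequency of morning stress (Aim 1), or of coping and positive affect (Aim 2). For adjustment, the Aim 2 section says: "Potential covariates for both models include number of ACEs, program compliance". It defines compliance as sessions attended and goes on to list coping mechanisms (by number and by type), age and sex.

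Under Demographics and program attendance: "Participants will report demographic characteristics (e.g., age, race/ethnicity, income) and previous weight loss history at baseline". Neither income nor previous weight loss history appears among the named covariates.

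Three other places bear on the point:
- Participants, eligibility, and recruitment notes that stress may affect whether people stay engaged in their program. Data management plan has attendance collected after Visit 4.
- The evening survey lists, among transient stressors, "conflicts with partner or children, and financial stress using checklist options".
- Sample size and power calculation allows up to five predictors at n = 50.

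**The concern.** In an observational cohort, the coefficient for stress variability depends on which pre-exposure common causes are controlled. Income is a natural candidate. It is recorded at the baseline visit, before momentary assessment starts the next day, and the article itself treats financial strain as a source of daily stress. If lower income goes with more variable stress and also with less weight loss, a model without it credits some of that pattern to variability, in the direction of Hypotheses 1a and 2.

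The named list uses its limited space differently. Sessions attended accrue after the exposure and, on the article's own account, may be affected by stress. Adjusting for a possible mediator does not control confounding and may remove part of the association of interest.

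The results are meant to inform whether a stress-focused momentary intervention is worth pursuing, so an association that partly reflects socioeconomic position would mislead that decision.

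**Working it through.** **Inputs**
- n = 50 (Participants, eligibility, and recruitment).
- Significance level 0.05 (Aim 2). Sidedness is not stated; two-sided is assumed.
- Up to five predictors (Sample size and power calculation).
- Correlation of income with stress variability, r(cx), and with weight loss, r(cy): not in the documents. Assumed 0.2 to 0.6 in absolute value, with signs such that lower income goes with more variability and less weight loss.

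**The plan's own figure.** The article states 0.80 power at n = 50 with effect size 0.3, alpha 0.01, critical R² 0.27 and five predictors. Reading 0.3 as the population R² in a random-predictor model, n = 50 gives power 0.773 and critical R² 0.2825. The smallest n reaching 0.80 is 53, with critical R² 0.268. The stated figure is narrowly missed, so there is no slack for extra terms: a sixth predictor lowers power at n = 50 to 0.729 and raises the required n to 56. These powers are for the overall test of R², not for the variability coefficient.

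**Predictor count.** Average, change frequency, ACEs, sessions attended, number of coping mechanisms, type of coping mechanism, age and sex make at least 8 terms, against 5 budgeted. Income has to replace listed covariates, not join them.

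**Size of the bias.** With standardised variables and no true effect, the expected spurious slope has absolute size r(cx) × r(cy). The false-positive rate was simulated with 20,000 replicates per cell in two set-ups: the exposure alone, and the exposure with four unrelated covariates (five predictors).

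| Both correlations | Spurious slope | Rate, exposure alone | Rate, five predictors | Rate, five predictors plus income |
|---|---|---|---|---|
| 0.2 | 0.04 | 5.9% | 5.8% | 4.8% |
| 0.3 | 0.09 | 9.7% | 8.9% | 5.1% |
| 0.4 | 0.16 | 19.9% | 19.1% | 5.2% |
| 0.5 | 0.25 | not run | 39.6% | 5.1% |
| 0.6 | 0.36 | not run | 70.0% | 4.8% |

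With income in the model the mean slope is zero to within simulation error.

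**When confounding alone would reach significance.** At n = 50 the two-sided 5% critical correlation is 0.279. The expected spurious association reaches it only when r(cx) × r(cy) = 0.279, which for equal correlations means √0.279 ≈ 0.53 each.

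**Cost of including income.** If income correlates 0.3 with the exposure and explains none of the outcome, the interval widens by 1/√(1 − 0.3²) = 1.048, about 5%.

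**The case against.** The strongest reply is that nothing has been left out. The list is introduced as potential covariates, it is open, and an analysis plan that is not shown may fix the final set. This stands as far as it goes: a reader might infer that the plan excludes income, and the documents do not say so. What remains is that the article names covariates, gives a place to a post-exposure variable, and does not name a socioeconomic one that it collects.

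Second, a reader might infer that income is an established common cause and that socioeconomic confounding would by itself produce the hypothesised result. The documents support neither. Nothing in them links income to weight loss. The financial-stress item is one evening checkbox among several, whereas the Hypothesis 1a exposure is morning stress. The incentive text, "Participants will also be eligible for a reduce initiation fee", concerns one program's fee and says nothing about income and outcome. The inflation is slight at correlations of 0.2, moderate at 0.3, and dominant only at about 0.5 or more.

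Third, the simulations leave out the week-0 average of the exposure, which is in the planned model, and treat the other covariates as unrelated to income. Average stress and ACEs may carry some of the income effect, so the tabulated rates could overstate the residual bias. This stands too.

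Finally, the aims are worded as associations and no treatment decision follows directly. That limits the severity, but an association meant to motivate an intervention still benefits from sensible confounder control.

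**Conclusion.** The point holds as an inexpensive improvement to the choice of covariates, not as an error that invalidates the analysis. It is documented that the cohort is observational, that income is collected at baseline and not named for the weight models, and that sessions attended are named although they follow the exposure and may be a mediator.

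The size is conditional. If income is a common cause with both correlations at 0.2, 0.3 or 0.4, omitting it gives false-positive rates of about 6%, 9-10% or 19-20% at n = 50, against about 5% with income included. This rests on assumed correlations, assumed signs, a two-sided test, no true effect, and no absorption by average stress or ACEs.

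**What to change.** Name baseline income, as a single ordinal or continuous term, as a fixed covariate in the Hypothesis 1a and 2 weight models. With one model per exposure, average, change frequency, age, sex and income make exactly the five predictors of the power calculation.

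Move sessions attended, coping mechanisms, ACEs and previous weight loss history to prespecified sensitivity models, and report the model without income as a further sensitivity analysis. ACEs precede the exposure and could be a confounder. Their move reflects the five-predictor limit and the article's own description of them, under Exploratory outcomes, as a potential mediator.

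The change is to wording only, since income is already collected. Compared with the same model without income, it costs one degree of freedom and about 5% in interval width in the unfavourable case shown above. Compared with entering all eight or more listed terms, it saves degrees of freedom: 50 − 5 − 1 = 44 residual against at most 50 − 8 − 1 = 41. With nine participants enrolled by January 2026, the choice can still be fixed before outcomes are analysed.

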#### Other stress-related states, and health behaviors.

As shown in Table 1, morning, signal-contingent, and evening surveys will assess other relevant considerations. The morning survey includes 16 questions, ending with the two questions that assess stress and coping. Participants will be asked, based on the previous night, how many hours of actual sleep they received, their bedtime and wake-time, and overall sleep quality. These questions are adapted from the Pittsburgh Sleep Quality Index, which is validated in adults [27]. This is followed by two questions on accelerometer and saliva compliance and then questions related to coping with stress and cravings the previous day. Cravings will be assessed using an adapted momentary scale of the Food Cravings Inventory (FCI). The FCI is questionnaire queries five different subscales including high fat foods, sweets, carbohydrates/starches, fast foods, and fruits and vegetables; this scale has been validated in adults [28]. FCI responses are via a 5-point scale, with higher scores indicating more frequent cravings. In the momentary question, we will ask how often they felt cravings for each of the 5-main items, with similar Likert scale responses. For example, they will be asked how frequent they craved carbohydrates/starches during the day. They will be asked if they indulged in cravings, and if so, which of the five craving groups with check box option.

**Table 1 pone.0357572.t001:** Daily Schedule of Ecological Momentary Assessment Surveys sent to participants for 14-days.

Construct	Morning Survey (8a-12p)	Period 1 (8a -11a)	Period 2 (11a -2p)	Period 3 (2p-5p)	Period 4 (5p-8p)	Evening Survey (6p-10p)
Sampling	Fixed	Random	Random	Random	Random	Fixed
*Stress and stress-related concepts*						
Acute Stress	x	x	x	x	x	x
Coping Mechanisms	x					x
Affect		x	x	x	x	
Chaos/ Disorder		x	x	x	x	x
Context		x	x	x	x	
*Health Behaviors*						
Diet	x					x
Cravings	x					x
Physical Activity						x
Sleep	x					
Survey Burden						x

Participants will also be surveyed about accelerometer wear at night and salivary cortisol collection in the morning survey, and accelerometer wear during the day will be queried in the evening survey.

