## Discussion

This study aims to examine potential pathways of stress and stress-related concepts with subsequent weight change and health behaviors during a behavioral weight loss intervention. Utilizing mHealth technology, assessing various forms of stress and through multiple modalities, and assessments in parallel to a behavioral weight loss program may help improve our understanding from cross-sectional or singular stress measures. The resulting data will inform if a much-needed EMI can support individuals as they engage in behavioral weight loss program in the real-world for lasting impact. Pending study findings, there are three main areas for future exploration. First, future studies may include examining similar constructs and outcomes amongst individuals using obesity-management medications; these medications are becoming more common [54] but individuals using these medications are excluded from enrolling in this study. Second, other considerations for future study may be examining other mental health constructs (e.g., depressive symptomology). The current study utilizes multiple questionnaires that are highly correlated with depressive symptoms (e.g., Perceived Stress Scale [40]), but does not directly address this construct. Finally, consideration of amount, types, and use of coping mechanisms may still require further exploration. It is possible that an individual with high coping ability, and thus lower variability, may still result in positive health behavior (e.g., physical activity and adequate sleep) [5,8]. Use of coping mechanisms may also improve as individuals engage in a behavioral weight loss program [5]. The current study addresses this concern by collecting additional details on coping mechanisms used at the individual and daily level.

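### The same-day stress model for Hypothesis 1b names no weekend or previous-night-sleep term, so day-to-day confounding could appear as a stress association

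*Protocol article*

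**What the plan says.** Under Analytical approach, Aim 1, the article states that "multi-level models with logit link function (and binomial distribution) will be used to examine association between week-0 morning stress and same day MVPA and sleep". The model is also to carry a product term, which the article words as "with an interaction of time/day*morning stress". It does not say whether day means the study day (1 to 14) or the day of the week. Nor does it say whether same-day sleep is the night just ended or the night to come.

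The covariates appear at the end of Aim 2: "Potential covariates for both models include number of ACEs, program compliance (i.e., number of sessions attended), coping mechanisms (number and type), age, and sex".

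The section on other stress-related states and health behaviors describes the morning survey. Participants report, "based on the previous night, how many hours of actual sleep they received, their bedtime and wake-time, and overall sleep quality". The order of items is also given: "The morning survey includes 16 questions, ending with the two questions that assess stress and coping". Sleep is therefore recorded before the exposure each morning. The Discussion adds that the study is "collecting additional details on coping mechanisms used at the individual and daily level", so coping might enter as a daily variable, but the version to be modelled is not stated.

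Lagged-day effects and marginal structural models are mentioned under Aim 1 as exploratory analyses, the latter only as something being considered.

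**The concern.** Hypothesis 1b is tested at the level of the day: does a more stressful morning go with less activity or sleep that day? A confounder of the day-to-day part of that association must itself change from day to day. ACEs, sessions attended, age and sex do not change over a 14-day window, so adjusting for them cannot remove confounding of this kind.

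Two things the study already records could move both stress and the outcome within a person. One is whether the day is a work day: 14 consecutive days always include weekends, and the signal-contingent surveys ask whether the participant is at home or at work. The other is the previous night's sleep, which comes before both the stress rating and that day's MVPA. If neither is in the model, a weekly rhythm or a bad night could be reported as a stress association. The article hopes its results may help justify a real-time stress intervention, so the distinction matters.

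**Working it through.** **Plan's own figure.** The article gives no figure on this point. Its sample-size statement (n = 50) concerns a person-level linear regression and has no bearing on day-level covariates in a logit model.

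**Level of each named covariate over the 14 days**

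| Covariate | Varies by day? |
|---|---|
| Number of ACEs | No |
| Sessions attended | No (one count per person) |
| Age, sex | No |
| Coping mechanisms | Possibly; version not stated |
| Weekend or non-work day | Yes; not named |
| Previous night's sleep | Yes; not named |

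**Mechanism.** Suppose stress has no effect. If a day-level factor Z shifts stress by a and the outcome by b, the within-person slope that omits Z is

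bias = a × b × Var(Z) / [Var(stress within person, given Z) + a² × Var(Z)].

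For a weekend indicator p = 2/7, so Var(Z) = 2/7 × 5/7 = 0.204. Assume a within-person stress SD of 1.8 points (variance 3.24); the documents give none.

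- Linear illustration: stress 1 point lower and sleep 45 minutes longer at weekends gives −1 × 45 × 0.204 / (3.24 + 0.204) = −2.7 minutes per stress point. The planned model is a logit model and does not yield minutes, so this shows the mechanism only.
- Log-odds scale, weekend: a = −1, b = +0.5 gives −0.102 / 3.444 = −0.030, or OR ≈ 0.97.
- Log-odds scale, previous-night sleep (per SD): a = −0.5, b = +0.4 gives −0.20 / (3.24 + 0.25) = −0.057, or OR ≈ 0.94.

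**Simulation with a binary outcome.** The setting was 50 persons × 14 days, true OR per stress point 1.00, and test level 0.05. The analysis was logistic GEE with exchangeable correlation, using person-mean-centred stress, the person mean and linear study day, first without and then with weekend and previous-night sleep. All confounder strengths are assumed.

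| Assumed confounding (a, b) | Runs | OR without | False positives without | False positives with both terms |
|---|---|---|---|---|
| None | 150 | 1.00 | 7% | 7% |
| Weekend weak (−0.5, +0.3) | 150 | 0.98 | 8% | 5% |
| Sleep weak (−0.3, +0.2) | 150 | 0.97 | 15% | 9% |
| Weekend moderate (−1, +0.5) | 400 | 0.96 | 15% | 8% |
| Weekend moderate, opposite sign (−1, −0.5) | 150 | 1.03 | 13% | 4% |
| Sleep moderate (−0.5, +0.4) | 400 | 0.93 | 33% | 6% |
| Both moderate | 400 | 0.91 | 55% | 6% |

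With 150 runs, the simulation error on a 5% rate is √(0.05 × 0.95 / 150) = 1.8 percentage points. The weak-weekend row therefore cannot be told apart from the row without confounding. With both terms added, the OR was about 1.00 in every setting. Linear study day was in the model throughout and did not remove the weekend bias.

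**The case against.** The strongest reply is that the article does not commit to the model criticised here. Much of that stands.

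- **The list is open.** It is worded as potential and as examples. A reader might infer that weekend and sleep terms have been ruled out; the text does not say so. Still, every example that can be clearly classified is person-level.
- **The list may not govern Hypothesis 1b.** It sits under Aim 2, its paragraph closes on the weight comparisons, and the power section refers to up to five predictors for a linear regression. If both models means the weight regressions, person-level covariates suit them, but then no confounder adjustment is named for Hypothesis 1b.
- **time/day may mean day of week.** Weekly rhythm would then be at least partly covered. One cannot assert that the term is only a linear trend. Previous-night sleep would remain unadjusted either way.
- **Person-level covariates are not useless.** No person-mean centring is stated, so the stress coefficient may mix between- and within-person association, and ACEs, age and sex can confound the between-person part.
- **Previous-night sleep is not automatically a covariate for sleep.** If same-day sleep is the night just ended, it is the outcome itself and precedes the stress rating.
- **Temporal ordering is recognised.** Lagged and marginal structural models are mentioned, but only as exploratory work, so they do not protect the main result.

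Hypothesis 1b also concerns secondary outcomes in an observational cohort, which limits the stakes.

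**Conclusion.** The concern holds as a gap in the stated model. For a day-level question, the article names covariates that are person-level apart from possibly daily coping, and it names neither of two plausible day-level confounders that it already measures. Day-level confounding could therefore appear as a stress association.

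A reader might go further and conclude that weekends and bad nights will be reported as a stress effect, or that a false-positive rate above 50% is to be expected. The documents do not support either conclusion. They give no confounder strengths, the bias reverses sign if weekends lower both stress and activity, and weak weekend effects leave the error rate near nominal. The simulated rates, about 8% to 55%, are illustrative and rest wholly on assumed values. The structural point does not depend on them: terms that are constant within a person cannot remove confounding that varies within a person.

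**What to change.** For the Hypothesis 1b models:

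1. State which covariates apply, and define day and same-day sleep.
2. Add a weekend/non-work-day indicator to both the MVPA and sleep models. For shift workers, base it on their own schedule, since a calendar weekend is a poor marker for them.
3. Add the previous night's sleep from the morning survey to the MVPA model. Add it to the sleep model only if the outcome is defined as the following night.
4. Split stress into the person mean and the daily deviation from it. Keep the person-level covariates for the between-person part.
5. Report the adjusted within-person stress coefficient as the Hypothesis 1b result.

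The cost is analysis-plan wording and a few degrees of freedom, out of at most 50 × 14 = 700 person-days at week 0. No new data are needed. Nine participants had been enrolled as of January 2026, so the change can still be fixed in advance of the analysis.
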